## Abstract

**Background:**

Fibromyalgia is a prevalent chronic rheumatic disease of great clinical importance. Recent studies have found raised levels of glutamate in the insula, hippocampus and posterior cingulate cortex regions of the brains of fibromyalgia (FM) patients. This finding has led researchers to speculate about the usefulness of glutamate-blocking drugs such as memantine in the treatment of fibromyalgia. The hypothesis of this study is that the administration of memantine will reduce the glutamate levels, and futhermore, will decrease the perceived pain. The aim of this study is to evaluate the efficacy of memantine in the treatment of pain (pain perception). A secondary objective is to evaluate the efficacy of memantine in the treatment of other clinical symptoms of FM, and to evaluate the efficacy of memantine in reducing brain levels of glutamate, and its effects on the central nervous system as a whole.

**Method/Design:**

A double-blind parallel randomized controlled trial. Participants, Seventy patients diagnosed with FM will be recruited from primary health care centers in Zaragoza, Spain. Intervention. The subjects will be randomized in two groups: A) A treatment group (n = 35), which will receive 20 mg of memantine daily; B) A control group (n = 35), to which will be administered a placebo. There will be a six-month follow-up period (including a titration period of one month). Outcomes. The main efficacy variable of this study is pain (pain perception). The secondary efficacy variables are clinical symptoms (pain threshold, cognitive function, health status, anxiety, depression, clinical impression and quality of life) and glutamate levels in different regions of the brain, which will be assessed by magnetic resonance spectroscopy. Randomization and blinding. Randomization has been computer-generated, and the random allocation sequence will be implemented by telephone. Subjects of the study and the research assistants will be blinded to group assignment.

**Discussion:**

There is a need for the development of innovative and more effective treatments for fibromyalgia. This clinical trial will determine whether memantine can be an effective pharmacological treatment for fibromyalgia patients.

**Trial registration:**

Current Controlled Trials
http://ISRCTN45127327 EUDRACT 2011-006244-73

## Background

Fibromyalgia (FM) is a chronic rheumatic disease of currently unknown aetiology that is characterized by the presence of diffuse musculoskeletal pain and painful sensitivity to touch in at least 11 of 18 defined trigger points
[1]. The prevalence of this syndrome in Europe is calculated to be approximately 2.9% (95% CI: 2.4 to 3.4)
[2]. The prevalence of FM in rheumatology consultations in Spain was found to be 12% (2.2% in men and 15.5% in women)
[3]. Because of its high prevalence, there is great clinical impact on patients in terms of disability and loss of quality of life, and significant health care costs. FM treatments are believed to have limited efficacy, with an effect size of approximately 0.5
[4].

Pain is the most common and debilitating symptom of FM. The cause of hyperalgesia in FM is poorly understood. It is suspected that there is an alteration of the function of structures of the central nervous system. In recent years, the neurophysiology of the phenomenon of pain has led to increased interest in employing different neuroimaging methods such as positron emission tomography (PET)
[5], single photon emission computed tomography (SPECT)
[6,7], functional magnetic resonance imaging (fMRI) and, more recently, magnetic resonance diffusion and diffusion tensor spectroscopy to identify the brain structures activated during episodes of pain in patients and controls
[8]. These structures include the primary and secondary sensory and motor cortices, insula, anterior cingulate cortex, thalamus, dorsolateral prefrontal cortex and basal ganglia - regions that have been named the ‘pain matrix’ because they are activated in response to a painful stimulus. A growing body of evidence suggests that glutamate (Glu), an excitatory neurotransmitter in the central nervous system, may play a part in the pathophysiology of FM, given that its concentration is elevated in the insula
[8], hippocampus
[9] and posterior cingulate cortex
[10,11].

As a consequence, a number of authors have suggested that glutamate-blocking drugs may be useful in the treatment of FM
[12]. Studies suggest that memantine could reduce the harmful effects that result from the excessively high levels of brain glutamate found in a number of conditions, such as FM
[13]. Memantine is not believed to act by reducing levels of glutamate or by preventing its release; rather, it is believed to reduce glutamate’s neurotoxic effect by blocking the N-methyl-D-aspartate (NMDA) receptor, thereby preventing the entry of excess calcium
[14]. Memantine belongs to the family of drugs known as NMDA receptor antagonists.

NMDA receptor antagonists have neuroprotective and analgesic properties and are widely used in clinical practice. Dextromethorphan and ketamine have demonstrated efficacy in the treatment of pain in fibromyalgia
[15,16], although their use as long-term treatment presents significant difficulties
[17]. The NMDA receptor antagonist memantine is a derivative of amantadine, a drug which has been used to treat Parkinson’s disease, spasticity, convulsions, vascular dementia and Alzheimer's disease, and has an excellent clinical safety record spanning more than 20 years. It is a non-competitive open-channel blocker that dissociates from the channel, which allows it to limit the pathological activity of the NMDA receptor without affecting normal synaptic activity
[18].

Memantine has shown a very low incidence of side effects in clinical trials on humans
[19,20], while a recent extension of trials has demonstrated the drug’s clinical tolerability, even with prolonged use
[21]. Similar low rates of adverse effects are expected with the treatment with memantine of other disorders such as pain
[22,23], migraine
[24] and fibromyalgia
[25]. The clinically approved dose of memantine for humans starts with 5 mg/day, increasing progressively over a period of several weeks to 20 mg/day. This progressive dose adjustment may contribute to the drug’s lack of side effects
[19]. While this progression reduces the NMDA receptor affinity, it contributes to the safety and efficacy of memantine as a neuroprotective agent. However, the process also makes memantine less effective than high-affinity antagonists (for example, ketamine) in the treatment of chronic pain
[21,26]. Nevertheless, recent research has highlighted the efficacy of memantine for the treatment of complex regional pain syndrome
[27] and phantom limb pain
[28], which suggests that the extent of analgesia depends on the type of pain being treated. We have carried out a preliminary open, uncontrolled, three-month follow-up study of memantine in patients with FM (EudraCT Number: 2011-000802-23). As will be commented later on in the discussion, in this preliminary study there was a trend toward improvement in pain, but it was not significant, probably due to the small sample size. Glutamate levels did not show modifications from baseline as a longer period follow-up is usually required. After three months, memantine-treated patients in our study showed significant improvement in cognitive function, symptoms of depression and global functioning (personal communication).

### Aims

The primary objective is to evaluate the efficacy of memantine in the treatment of pain (pain perception) in patients with fibromyalgia.

The secondary objectives of this study are the following: 1) To evaluate the efficacy of memantine in the treatment of other symptoms of fibromyalgia, such as pain threshold, impaired cognitive function, reduced health status, anxiety, depression, quality of life and perceived improvement of symptoms; 2) To evaluate the efficacy of memantine in reducing brain levels of glutamate, as measured by spectrometry, in patients with fibromyalgia.

## Methods

### Study design

Doubled-blind, multicenter, parallel randomized clinical trial with six-month follow-up.

Seventy patients with FM will be recruited for inclusion in the study upon fulfilment of selection criteria. The patients will be randomized in two parallel groups: a treatment group (n = 35), which will be given 20 mg of memantine daily; a control group (n = 35), which will receive a placebo. There will be a six-month follow-up period (including a dose adjustment period of one month). The study flowchart is shown in Figure 
1.

**Figure 1 F1:**
[figure not shown]
Flowchart of the study.

### Setting and study sample (Participants)

Patients diagnosed with FM will be recruited for inclusion in the study from primary health care centers in Zaragoza, Spain, upon fulfilment of the following selection criteria: a) subject (males and females) with age between 18 and 65 years; b) ability to understand Spanish; c) diagnosis of FM performed by a rheumatology specialist according to the American College of Rheumatology (ACR 1990) diagnostic criteria; d) signing of an informed consent form; and e) use of birth control during the study in the case of fertile women.

Patients must not fulfil any of the following criteria at the time of inclusion: a) be undergoing drug treatment for fibromyalgia. In these cases, the patients will discontinue treatment and go through a washout period of one week to minimize the influence of the medication on brain imaging. During that week, the patient may take, if necessary, low doses of analgesics such as tramadol or paracetamol; b) be taking memantine, or have taken memantine during the one year prior to recruitment; c) be suffering from an Axis I psychiatric disorder, as diagnosed using the Structured Clinical Interview for DSM-IV (SCID-I), that might hinder adherence to the protocol (for example, dementia, alcohol and/or substance abuse/dependence, or schizophrenia); d) be pregnant or breast-feeding; e) have a hypersensitivity to the active ingredient memantine, or to the excipients; f) have conditions that require special precautions when administering memantine according to the summary of product characteristics (namely, epilepsy, circumstances that may cause high urinary pH such as *Proteus* urinary infection, renal tubular acidosis or vegetarian diet, recent myocardial infarction, congestive heart disease and uncontrolled arterial hypertension); g) have clinically significant and active evidence of liver or kidney disease, hematological, respiratory, endocrine or cardiovascular disease or disorders. However, patients with controlled diabetes, controlled hypertension and complete or incomplete right bundle branch block can be included in the study; h) use drugs that may cause relevant interactions with memantine according to the summary of product characteristics, namely NMDA receptor antagonists (for example, amantadine, ketamine, dextromethorphan), L-Dopa, dopamine agonists and cholinergic agonists; or i) use non-permitted concomitant medication during the week prior to the first evaluation visit or be expected to require treatment with at least one of the drugs not permitted during the study, namely, antidepressants (for example, duloxetine, venlafaxine, mirtazapine, bupropion, SSRIs, and so on), analgesics (for example, pregabalin, gabapentin, opiates, and so on) or other drugs. During this week, patients may take analgesics such as tramadol or paracetamol if needed, but only sporadically to minimize the influence of the medication on brain images.

There is currently no approved treatment with an indication for the treatment of FM. In 2007, the FDA approved pregbalin as the first drug for the treatment of FM symptoms in the USA. This agency has subsequently approved duloxetine and milnacipran for the same indication. Although these drugs are commercially available in Europe with other indications, European regulatory authorities have recently refused to widen their approval to include them for the treatment of FM
[29].

A patient is to withdraw from the trial if he or she withdraws informed consent, if the researcher feels that he or she should withdraw from the study for reasons of safety/efficacy or in the best interest of the patient, or if the patient does not comply with the treatment for more than seven consecutive days.

### Intervention

#### Treatment group

The treatment group will receive the study drug, memantine, in a dose of 20 mg daily for six months, including a one-month titration period.

#### Control group

The control group will receive a daily dose of placebo (coated pills with the same external appearance as the active drug) and will take the same number of pills as the treatment group. Administration will be through the oral route.

This is a double-blind study. Consequently, the patients will be randomized, and neither the patient, the doctor nor the researcher administering questionnaires or spectrometry will know to which group the patient has been assigned. The recommended dose of memantine in adults is 20 mg once a day. To minimize adverse effects, 20 mg doses will be reached by the following titration schema: first week, 5 mg daily; second week, 10 mg daily; third week, 15 mg daily; fourth week, 20 mg daily.

The number of tablets in each dispensed container will be monitored at each evaluation, keeping track of the number the patient should have taken and how many should remain on completion of the treatment. The route of administration is oral, in the form of film-coated tablets. The drug for use in the study (both memantine pills and placebo) will be prepared, conditioned and released by one qualified person according to the principles of Good Manufacturing Practice, under the responsibility of H Lundbeck A/S. Upon completion of the trial, patients will continue with standard FM treatment according to clinical practice guidelines.

### Outcomes and measurements

#### Main outcome variables

The main efficacy variable is the improvement in the treatment of pain, specifically pain perception. Perceived pain will be measured by means of a visual analogue scale (VAS) from 0 to 100. The psychometric usefulness of VAS has been widely demonstrated
[30].

#### Secondary variables

Secondary efficacy variables are modifications made to values of the following clinical variables: pain threshold, cognitive state, health status, state of anxiety and depression, clinical improvement impression and quality of life.

Pain threshold will be measured by means of a sphygmomanometer, a widely used clinical test that has been demonstrated to be useful for identifying FM patients
[31]. It is recommended that the blood pressure cuff should be inflated in increments of approximately 10 mmHg up to 180 mmHg or to the point that pain appears. Healthy persons tend to feel pain when the pressure cuff is inflated to 160 mmHg or more, while FM patients generally present pain at pressures between 100 and 110 mmHg, or even lower. Blood pressure should be recorded to adjust for the effect of hypertension on pain threshold.

The rest of the secondary efficacy variables will be measured by structured exams. The Cognition Mini-Exam (MEC) will measure cognitive state. The MEC is a structured scale that consists of 35 points grouped into seven categories: orientation to place, orientation to time, recall, attention and concentration, memory, language and visual construction. In non-geriatric populations (under the age of 65) such as the sample for this study, the threshold that suggests a ‘likely case’ of a cognitive disorder is 27 points and lower. This test is the validated Spanish-language version of the Mini-Mental State Examination (MMSE)
[32].

Health status in FM will be measured by means of the Fibromyalgia Impact Questionnaire (FIQ). The FIQ is a ten-item self-assessment questionnaire that measures the health status of FM patients. The validated Spanish-language version of this questionnaire will be used
[33]. Anxiety and depression will be measured by means of the Hospital Anxiety Depression Scale (HADS). HADS is a scale based on self-report that was developed to detect the presence of depression and anxiety disorders in medical patients in primary care settings. It contains fourteen items scored on a four-point Likert-type scale. This scale is comprised of two subscales that separately assess depression and anxiety. The validated Spanish-language version of this scale will be used
[34]. Quality of life will be measured by means of the EuroQol 5D (EQ5D) questionnaire. This questionnaire is a standardized instrument used as a measure of health outcomes. It is applied to a wide range of health conditions and treatments and provides a simple descriptive profile and a single index value for health status. The Spanish-language version of this questionnaire will be used
[35]. Perceived clinical improvement will be assessed by the Clinical Global Impression scale (CGI).


Table 
1 shows the procedure and evaluation times of the trial.

**Table 1 T1:** Procedure and evaluation times of the trial

**Visit**	**Baseline**	**1 month**	**3 months**	**6 months**
Visit number	1	2	3	4
**Recruitment & Clinical assessment**				
Signing of informed consent	X			
Diagnosis	X			
Inclusion/exclusion criteria	X			
Sociodemographic variables	X			
Pain assessed with sphygmomanometer	X	X	X	X
Pain assessed with Analogue Visual Scale	X	X	X	X
Cognitive function (assessed with MEC)	X	X	X	X
Global function (evaluated by FIQ)	X	X	X	X
Anxiety and depression (assessed with HADS)	X	X	X	X
Quality of life (assessed by EuroQol 5D)	X	X	X	X
Clinical Global Impression (CGI)	X	X	X	X
**Neuroimage assessment**				
Magnetic resonance spectroscopy	X			X
**Safety assessments**				
Adverse events		X	X	X
**Other study procedures**				
Delivery of the research drug	X	X	X	
Inventory of drug taken back and used		X	X	X
Concomitant pharmacological treatment	X	X	X	X

### Sample size

The choice was made to have a sample comprising 70 subjects (n = 35 subjects in each of the two treatment groups) because this sample size will enable us to obtain reliable results and to ensure that both treatment groups are of equal sizes at the start of the study. Smaller sample sizes have been used in the identification of significant differences in glutamate levels in different brain regions between FM patients and controls.

Using the results of the pilot study and taking reduction of pain (as determined using the Pain Visual Analogue Scale and sphygmomanometry) as the primary variables, a pre-intervention mean score of 56 (SD 14.9) was obtained with the VAS, and 104 (SD 30.8) with sphygmomanometry. After treatment, the means decreased to 44 (SD 16.9) and 85 (SD 20.6), respectively. Therefore, assuming a 95% confidence interval and a power of 80%, we find that we require a sample size of 28 individuals in each group for the VAS finding and of 30 individuals in each group for the reduction measured by sphygmomanometry. The resulting sample size that will enable us to analyse the final variable will be 60 individuals, with 30 being assigned to each of the two groups. Based on previous studies (personal communication), an attrition rate of 10% can be expected. Therefore, the final number of recruited patients will be 35 patients for each arm.

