### Statistical methods

#### Analysis strategy

The analysis of clinical efficacy will make use of intention-to-treat analysis. The Last-Observation-Carried-Forward (LOCF) method will be used for handling missing data. An initial comparison will be made between both groups, examining key variables to establish the groups’ baseline comparability after randomization. To describe the quantitative variables, means and standard deviations will be calculated when they fulfil normality criteria. The Chi-squared test will be used for qualitative variables such as a number of socio-demographic ones. The differences between clinical variables at baseline, one month, three months and six months will be calculated using analysis of covariance (ANCOVA) adjusted by baseline.

To study the main variable, analysis of variance will be performed on repeated measurements, including all the evaluations over time. The main variable (pain perception) will be taken to be a continuous variable for this purpose. The models will include adjustments for the baseline pain value and for any other variable that may have shown differences in the baseline measurement. Possible group × time interactions will be studied by means of Mixed Factor ANOVA. Additionally, linear regression models will be used to compare the differences between the two groups for each of the evaluations over time as compared to baseline. Similar analyses will be performed on the other secondary clinical variables.

To analyze the differences found by the neuroimaging test (spectrometry) taken at baseline and at six months follow-up, Student’s *t*-test for paired measurements will be calculated. The relation between neuroimaging variables and clinical variables will be assessed by means of Spearman’s Rho non-parametric test.

In case of lost values, a sensitivity analysis will be made to estimate the effect of the lost values on the results. These values will also be replaced using several approaches, such as last recorded values and imputations. Statistical analyses will be performed with the Statistical Package for the Social Sciences (SPSS) 19.0 statistical software package (SPSS Inc., [name]), with *P-*values below 0.05 considered significant.

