## Discussion

This is the first randomized, controlled study of memantine for the treatment of fibromyalgia. Memantine might be expected to be useful for the treatment of FM based on its pharmacological effects, as described in the introduction
[13,14]. In addition, our research group have recently carried out an exploratory, uncontrolled study with a small sample (n = 10) and a three-month follow-up that found significant improvement of global function (as measured by FIQ), depression (as evaluated by HADS) and cognitive function (as assessed with MEC) in the study patients at three-month follow-up (personal communication, Study EudraCT Number: 2011-000802-23). However, at three-month follow-up, glutamate levels did not decrease in any of the brain areas studied (personal communication).

Based on previous preliminary pilot studies (personal communication) a significant improvement in key clinical symptoms in fibromyalgia, such as depression, cognition and global function can be expected. Cognition is one of the most impairing symptoms in fibromyalgia
[36] and is strongly correlated with depression
[37]. Cognition in these patients seems to be related to brain morphology changes that could be improved with memantine
[38]. Depression, another frequent and quite disabling symptom in fibromyalgia
[39] is also expected to improve with memantine due to its pharmacological effect
[40].

Pain, the most relevant symptom in fibromyalgia and the main outcome of our study, was not significantly relieved in our open, uncontrolled study (personal communication), probably due to its small sample size. However, previous pilot studies (26 to 28) suggest memantine is effective in relieving pain in general. In addition, spectrometric studies in fibromyalgia found a strong correlation between high levels of glutamate and depression and global function, but also with pain (10).

Treatment with memantine decreases the Glu/Cr (glutamate/creatine) ratio in the left hippocampal region, which may account for its anti-excitotoxic property
[41]. Other studies have observed an increase in cingulate glutamatergic turnover
[42]. There is evidence from MRS studies of other excitotoxicity-related conditions, such as amyotrophic lateral sclerosis
[43] and Huntington’s disease

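### The 80% power claim uses the before-and-after change of one uncontrolled pilot group as the memantine–placebo difference, so it is supported only if placebo patients improve little or not at all

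*Protocol article*

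**What the plan says.** The Sample size section reports pilot values before treatment, "a pre-intervention mean score of 56 (SD 14.9) was obtained with the VAS, and 104 (SD 30.8) with sphygmomanometry", and then after it: "After treatment, the means decreased to 44 (SD 16.9) and 85 (SD 20.6), respectively". From these, "assuming a 95% confidence interval and a power of 80" per cent, it concludes: "we require a sample size of 28 individuals in each group for the VAS finding and of 30 individuals in each group" for sphygmomanometry. The larger figure sets 30 evaluable patients per arm, and an expected 10% attrition takes recruitment to 35 per arm. The section gives no expected placebo change and no memantine–placebo difference.

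The Background and Discussion describe the pilot as open and uncontrolled, with ten patients and three months of follow-up. The Discussion says that pain "was not significantly relieved in our open, uncontrolled study". The trial itself is double-blind and placebo-controlled, with six months of follow-up. On the size of effect seen in this field, the Background says: "FM treatments are believed to have limited efficacy, with an effect size of approximately 0.5".

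The Analysis strategy section plans intention-to-treat analysis with last observation carried forward, adjustment for baseline pain, and P "values below 0.05 considered significant".

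**The concern.** A change within one treated group is not a difference between two randomised groups. It contains the drug effect together with anything that would also have happened on placebo: placebo response, regression to the mean, and any recovery after prior fibromyalgia medication is stopped for the one-week washout. In the trial these components arise in both arms and cancel in the comparison. Using the full pilot change as the target difference assumes that they sum to zero.

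This is the only power justification for the primary outcome. If the assumption fails, the chance of detecting a real but smaller benefit is below the stated 80%, and the document gives no way to see by how much.

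**Working it through.** **Inputs (Sample size section).** VAS 56 (SD 14.9) to 44 (SD 16.9), a fall of 12. Sphygmomanometry 104 (SD 30.8) to 85 (SD 20.6), a fall of 19 mmHg. Power 80%, alpha 0.05. Sidedness is not stated, but only the two-sided version matches.

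**Reproducing the plan's figures.** For two independent groups, n per group = (1.96 + 0.8416)² × (SD₁² + SD₂²) / difference².

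- VAS: 7.849 × (14.9² + 16.9²) / 12² = 7.849 × 507.62 / 144 = 27.67, so 28, as stated.
- Sphygmomanometry: 7.849 × (30.8² + 20.6²) / 19² = 7.849 × 1373.0 / 361 = 29.85, so 30, as stated.

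One-sided versions give 22 and 24. A paired formula with a positive correlation gives fewer (VAS about 14 at r = 0.5). So the pilot's before value served as the control-arm mean and its after value as the memantine-arm mean. For VAS, this holds placebo at 56 throughout.

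**Implied effect.** Pooled VAS SD = √(507.62 / 2) = 15.93, and 12 / 15.93 = 0.75 SD. For sphygmomanometry, SD = √(1373.0 / 2) = 26.20, and 19 / 26.20 = 0.73 SD.

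**Power if placebo also improves.** The net difference is 12 minus the placebo fall. The placebo fall is an assumption, so a range is shown. Power is from the noncentral t with noncentrality net / (SD × √(2/n)), two-sided 0.05. For the baseline-adjusted analysis the SD becomes 15.93 × √(1 − r²), which is 14.23 at r = 0.45 and 11.38 at r = 0.7, with one degree of freedom fewer. Both correlations are assumed.

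| Analysis | n per arm | Net 12 | Net 10 | Net 8 | Net 6 | Difference detectable at 80% |
|---|---|---|---|---|---|---|
| Unadjusted | 30 | 81.8% | 66.7% | 48.1% | 30.0% | 11.7 |
| Unadjusted | 35 | 87.4% | 73.5% | 54.4% | 34.2% | 10.8 |
| Adjusted, r = 0.45 | 30 | 89.5% | 76.3% | 57.2% | 36.2% | 10.5 |
| Adjusted, r = 0.45 | 35 | 93.5% | 82.6% | 64.0% | 41.3% | 9.7 |
| Adjusted, r = 0.7 | 30 | 98.0% | 91.7% | 76.3% | 51.9% | 8.4 |
| Adjusted, r = 0.7 | 35 | 99.2% | 95.2% | 82.6% | 58.5% | 7.7 |

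Taking 12 minus the last column, the placebo fall that still leaves 80% power is 0.3, 1.2, 1.5, 2.3, 3.6 and 4.3 points, row by row.

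**Illustration at 0.5 SD.** If the Background's general effect size were a between-arm VAS effect, unadjusted power would be 48% with 30 per arm and 54% with 35.

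**The case against.** The strongest reply is that the plan has cushions which the sample size calculation does not count. The intention-to-treat rule with last observation carried forward can keep up to 35 per arm in the analysis, and adjustment for baseline pain is planned. This stands. A reader might infer that the 80% fails as soon as placebo patients improve at all, or that the trial is simply underpowered. The documents do not support either. With 35 analysed, 80% survives a placebo fall of 1.2 points unadjusted, 2.3 at r = 0.45 and 4.3 at r = 0.7.

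It is tempting to cap that help by arguing that a non-significant ten-patient pilot rules out a correlation above 0.45. It does not. The bound assumes a paired t-test, and the document names no test. It also limits only the correlation observed in those ten patients: a sample value of 0.449 at n = 10 has a Fisher 95% interval of about −0.25 to 0.84.

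The Background's 0.5 is a general remark. It does not say whether it concerns pain, drugs or a comparison with placebo, so the 48% and 54% are illustrations, not a contradiction within the document. Nor does any passage say that a null result would be taken as proof of no effect.

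What the reply does not reach is the input itself. No section replaces the pre-post change with a between-arm difference, and the stated calculation claims no benefit from baseline adjustment. The cushions are also limited: at a net difference of 6 points, power stays below 60% in every scenario shown. Nor is this detail left to a fuller protocol, since the calculation is stated and its inputs are visible.

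**Conclusion.** The concern holds. That both sample sizes rest on treating one uncontrolled group's before and after values as two arms is established by exact reproduction. The 80% is therefore unsupported as a statement about memantine against placebo, and it holds only if placebo patients improve little or not at all.

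The size of the shortfall is conditional. It ranges from none, if placebo does not move, to a severe loss if placebo patients gain half of the pilot change (net 6 points: 30% unadjusted with 30 per arm, 59% with 35 analysed and an assumed r of 0.7). All these figures rest on the pilot SDs, which come from ten patients at three months, and on assumed placebo changes and correlations. The type I error rate and the treatment estimate are not affected. This should be fixed, but it is a fault in the justification and not in the design or analysis.

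**What to change.** Keep the sample size and rewrite the justification:

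- Replace the 80% claim with the between-arm VAS difference detectable at 80% power: 11.7 points with 30 per arm and 10.8 with 35, unadjusted; 10.5 and 9.7 with baseline adjustment at an assumed r of 0.45; 8.4 and 7.7 at an assumed r of 0.7.
- Tabulate power by net difference for the planned baseline-adjusted analysis, over a stated range of correlations and for both 30 and 35 analysed.
- Label the 12 points and 19 mmHg as uncontrolled pre-post changes that make no allowance for placebo response.
- Withdraw the sphygmomanometry-based 30 per group, or restate it in the same way, since it is the figure that sets the sample size.
- Commit to interpreting a non-significant result by its confidence interval.

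The cost is a change of text, and the stated power becomes less favourable. No extra patients are needed, and neither the design nor the analysis changes.
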